#### Baseline Assessments

- Baseline prescribing rates
- Baseline survey to assess provider characteristics and provider attitudes toward practice guidelines, clinical decision support, electronic health records, and practice environment.

#### Randomization

We will implement a cluster-randomized design at the clinic level to avoid contamination that might occur if individual providers in close proximity are randomized to different interventions. Providers who practice at multiple clinics will be assigned to the intervention of the clinic for which they spend at least 85% of their time. Geographically distinct individual clinics will be the unit of randomization. We will conduct a block randomization of clinics by clinic organization.

## **7. SAFETY ASSESSMENTS**

Data for patients who have a return visit to a study clinic within 30 days of an eligible study visit with a diagnosis that could represent a serious complication of an untreated bacterial infection (e.g. acute rheumatic fever, head and neck abscess, intracranial abscess, Lemierre syndrome,

mastoiditis, meningitis, pneumonia, sepsis, etc.) will be extracted from study site EHRs and reported to the Data Safety and Monitoring Board.

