### **7.1 Specification of Safety Parameters**

Data elements from qualifying ARI visits for providers enrolled in the study will be collected from the electronic health record. At Partners Healthcare, total qualifying visits will be based on qualifying ICD-9 codes (See Appendix E: Code Set Definitions), while Los Angeles sites also incorporate exclusions of suppressor codes used in the decision to trigger the clinical decision support. Aggregate counts of total ARI visits across sites for which the intervention was triggered, including those for which an antibiotic was not prescribed, and the number of return visits occurring within 30 days of index visits (and associated rate of return) with a diagnosis of concern (See Appendix E for diagnoses of concern at revisit) will be calculated. Of return visits identified with a diagnosis of concern, a random sample of 20% of cases will be generated for chart review by site physicians to determine the possibility of study interventions interfering with proper diagnosis and treatment of a patient. Cases will be examined to determine whether earlier antibiotics would have improved the outcomes and classified as one of the following: earlier antibiotics UNLIKELY to have improved the course, early antibiotics MAY HAVE improved the course, UNCERTAIN if earlier antibiotics would have improved the course.

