### **7.3 Adverse Events**

Adverse events are defined as the number of return visits occurring within 30 days of index visits (and associated rate of return) with a diagnosis of concern (See Appendix E for diagnoses of concern at revisit).

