geographic area in either Massachusetts (Partners Healthcare consisting of Brigham and Women's Hospital and Massachusetts General Hospital affiliated primary care practices) or Southern California (AltaMed; The Children's Clinic). We will carry out a block randomization of clinics by clinic organization using the statistical computing language R. We first will construct two matrices that each represent a main effects design and together represented the full factorial design ( $2 \times 2 \times 2$  design). For each clinic organization, we will construct ordered collections of clinics. We then will employ the sample function in R to return a random permutation of each ordered collection. For each collection of clinic organizations we will draw a sample that represents the largest number of clinics within each clinic organization that was divisible by 8, the number of study arms. We then will use the list function, a function that ties together related data that do not share the same structure, to assign each randomly permuted clinic to a study arm, repeating this process until clinics have filled the eight arms of the study in equal measure. Because the number of clinics at each organization is not always divisible by eight, we will treat "remainder" clinics across all organizations differently. These remainder clinics will be randomized to conditions within one of the fractional factorial main effects design (a subset of the larger  $2 \times 2 \times 2$  design) to maximize power for main effects estimates. This will be accomplished in a procedure similar to the one described above. One of the two possible fractional factorial designs of the larger  $2 \times 2 \times 2$  design will be chosen randomly to assign remainder clinics to a condition so that remainder clinics have an ex ante equal probability of assignment to any one of the eight conditions in the full factorial design. Allocation of the sequence will be concealed until after the interventions were assigned.

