### 10.2 Data Management

Each of the participating sites will create an extract from their Electronic Medical or Billing Records of the Data Elements for all patients with an upper respiratory infection. These records will be transferred to the coordinating center on a weekly basis.

The CC has created programs and quality control queries for transforming all of the data into a standard model (Observational Medical Outcomes Partnership Common Data Model, version 3).

The data collection forms will be online surveys. Each of the electronic data systems, Epic, NextGen, and the Longitudinal Medical Record and Partners Healthcare billing system will have native data capture formats.

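### The rate of serious complications sent to the safety board is biased downward, because Sections 7 and 9.3 count only returns to a study clinic and Sections 7.1 and 7.3 leave the place open

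*Protocol*

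**What the plan says.** Section 7 bases the safety data on "Data for patients who have a return visit to a study clinic within 30 days of an eligible study visit". It adds that these data "will be extracted from study site EHRs and reported to the Data Safety and Monitoring Board". Section 9.3 repeats the study-clinic condition when it describes what the board receives. The examples in both places include intracranial abscess and run on to "mastoiditis, meningitis, pneumonia, sepsis, etc".

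Section 7.1 gives the operational measure as "the number of return visits occurring within 30 days of index visits (and associated rate of return) with a diagnosis of concern". Section 7.3 reads "Adverse events are defined as the number of return visits occurring within 30 days of index visits". Neither says where the visit must take place.

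Of the returns found in this way, "a random sample of 20% of cases will be generated for chart review by site physicians" (Section 7.1). Separately, Section 7.4 has the principal investigator report unanticipated events to the IRB and the board, which then meets to decide on continuation.

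Section 4.1 requires each study clinic to occupy its own building, and gives a hospital floor as an example of what does not qualify. On data, Section 9.2.1 refers to "Massachusetts General Hospital affiliated primary care practices", and Section 10.2 says that the listed record systems and the "Partners Healthcare billing system will have native data capture formats". No section names emergency department, inpatient or death records as a source of safety events.

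**The concern.** The trial sets out to reduce antibiotic prescribing, so untreated bacterial infection is its main safety question. Several of the complications listed are ones that a patient may take straight to an emergency department or hospital. The sites are outpatient practices, and the count depends on the patient coming back to one of them.

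Consider a patient seen on day 0, admitted with meningitis on day 5, and still in hospital or dead on day 30. Under Sections 7 and 9.3 that patient has no event. The graver the complication, the smaller the chance that it enters the count. The board reviews patient safety and advises whether the study should continue, so a reassuring figure could reflect where events were sought as much as how often they occurred.

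**Working it through.** The protocol states no expected complication rate, safety margin or safety power, so there is no planned figure to reproduce. The check is a comparison of the sections, followed by an illustration on assumed inputs.

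**Step 1: where an event must occur to be counted**

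| Section | Place of the return visit | Source |
|---|---|---|
| 7 | Study clinic | Study site EHRs |
| 9.3 | Study clinic | Study site EHRs |
| 7.1 | Not stated | EHR, for qualifying ARI visits of enrolled providers |
| 7.3 | Not stated | Not stated |

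The two sections that name a place agree, and nothing in 7.1 or 7.3 widens it. The natural reading is the narrow one.

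**Step 2: what is captured under that reading**

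- Treated at a study clinic within 30 days: counted.
- Treated in an emergency department or hospital, then a study-clinic visit by day 30 carrying the diagnosis: counted.
- Treated in an emergency department or hospital, no such visit by day 30: not counted.
- Death, or an admission lasting to day 30, with no earlier clinic visit carrying the diagnosis: not counted.

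**Step 3: whether another route repairs the rate**

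- The 20% chart review samples returns already identified, so it cannot find an event with no return.
- Reporting under Section 7.4 has no clinic condition, but no active search is described and its cases do not enter the rate defined in 7.1 and 7.3.

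**Step 4: size, on assumptions**

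Let t be the true 30-day rate per index visit and c the share of events that produce a study-clinic visit carrying the diagnosis by day 30. The protocol gives neither. Then reported rate = t × c, and counted events = N × t × c. N = 4,504 is the visit total required in Section 9.2; it serves only to scale the illustration.

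| Assumed t | Expected events (N × t) | c = 75% | c = 50% | c = 25% |
|---|---|---|---|---|
| 0.1% | 4.5 | 3.4 | 2.3 | 1.1 |
| 0.5% | 22.5 | 16.9 | 11.3 | 5.6 |
| 1.0% | 45.0 | 33.8 | 22.5 | 11.3 |

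For t = 0.5% and c = 50%: 4,504 × 0.005 × 0.50 = 11.3 events, a reported rate of 0.25%.

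**Step 5: ratio against absolute rate**

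If c is the same in two arms with rates p1 and p0, the ratio (p1 × c)/(p0 × c) = p1/p0 is unchanged, while the difference (p1 − p0) × c shrinks. With assumed rates of 1.0% and 0.5% the ratio stays at 2.0, and the difference falls from 0.5 to 0.125 percentage points at c = 25%.

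Fewer events also cost power. With 2,252 visits per factor level, one-sided 0.05 and no clustering correction, power is approximately Φ[(p1 − p0)/√((p1(1 − p1) + p0(1 − p0))/2,252) − 1.645].

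- c = 100%: 0.005/0.00257 = 1.946, giving 62%.
- c = 25% (0.25% against 0.125%): 0.00125/0.00129 = 0.970, giving 25%.

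Clustering would lower both figures.

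**The case against.** **Hospital-treated cases are not lost by definition.** A reader might infer that every case treated in hospital is missed. The text does not support that: a follow-up visit to the study clinic by day 30 with the diagnosis coded is enough, and some patients will have one. The list also includes conditions such as pneumonia that a clinic may see itself. This limits the size of the bias but does not remove it.

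**The wording is not uniform.** Sections 7.1 and 7.3 carry no clinic restriction, so the sponsor may have meant something wider. That is fair, but then Sections 7 and 9.3 contradict the intent and still need correcting.

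**The board has another route.** A reader might infer that the decision to continue rests on this rate alone. It does not, because Section 7.4 lets any unanticipated event reach the board. What stands is that this route is passive and leaves the reported rate unchanged.

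**Equal under-capture preserves the comparison between arms.** True for a ratio, and nothing in the protocol shows that capture differs by arm. But Section 7.1 plans aggregate counts and a rate of return for visits where the intervention was triggered, and no arm comparison of these complications. The figure the board sees is the absolute one, which is the one affected.

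**Wider data may not be available.** Hospital affiliation and mention of a billing system do not prove that hospital encounters are in the extract, and no hospital is named for the two California organisations. This stands, and the fix has to allow for it.

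**Conclusion.** The point holds in this form: as written in Sections 7 and 9.3, serious complications treated elsewhere are missed unless a coded study-clinic visit follows by day 30, and the absolute rate reported to the board is biased downward. Deaths and long admissions are the least likely to be captured. The direction follows from the definition, provided that at least some events lead to no such visit. The size cannot be computed from the protocol; the reported rate is c times the true rate, and any value of c is an assumption.

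The protocol does not show that all hospital-treated cases are lost, that the arms are affected differently, or that the interventions are unsafe. The conclusion rests on reading 7.1 and 7.3 in line with 7 and 9.3. If the sponsor intended the wider reading, what remains is a contradiction to resolve and a data source to name.

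**What to change.** Reconcile Sections 7, 7.1, 7.3 and 9.3 with one definition: any encounter (clinic, urgent care, emergency department or inpatient) or recorded death within 30 days of the index visit, with a diagnosis of concern, that is visible in the participating organisation's existing EHR or billing records.

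Report counts by organisation and by arm. Where an organisation's records hold no hospital encounters, say in the board report that its figure covers clinic returns only.

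**Cost.** If hospital encounters are already held, the change is a wider encounter filter on an extract that Section 10.2 already transfers weekly. Whether they are held is an assumption to check with each organisation first. Section 6.2.1 describes clinicians' permission as covering records of patients who saw them for ARIs, so the IRB wording on data elements may need to be extended. If no hospital records are available, the cost is one sentence in the report.

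**Downside.** Completeness will differ between organisations. Section 9.2.1 blocks on organisation but pools the remainder clinics across organisations, so balance within each organisation is not exact. Any arm comparison should be made within organisation and read with caution. No treatment rule changes.

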### **7.1 Specification of Safety Parameters**

Data elements from qualifying ARI visits for providers enrolled in the study will be collected from the electronic health record. At Partners Healthcare, total qualifying visits will be based on qualifying ICD-9 codes (See Appendix E: Code Set Definitions), while Los Angeles sites also incorporate exclusions of suppressor codes used in the decision to trigger the clinical decision support. Aggregate counts of total ARI visits across sites for which the intervention was triggered, including those for which an antibiotic was not prescribed, and the number of return visits occurring within 30 days of index visits (and associated rate of return) with a diagnosis of concern (See Appendix E for diagnoses of concern at revisit) will be calculated. Of return visits identified with a diagnosis of concern, a random sample of 20% of cases will be generated for chart review by site physicians to determine the possibility of study interventions interfering with proper diagnosis and treatment of a patient. Cases will be examined to determine whether earlier antibiotics would have improved the outcomes and classified as one of the following: earlier antibiotics UNLIKELY to have improved the course, early antibiotics MAY HAVE improved the course, UNCERTAIN if earlier antibiotics would have improved the course.

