### **9.3 Interim analyses and Stopping Rules**

No interim analysis will be conducted on primary or secondary outcomes. The Data Safety and Monitoring board is granted the power to recommend discontinuation of the study to each study IRB, if safety concerns are found. The board will meet biannually throughout the duration of the study to review patient safety and adverse events. Following each meeting, the board will make recommendations to the local IRBs as to whether the study should continue or if changes to the protocol are needed. Data for patients who have a return visit to a study clinic within 30 days of an eligible study visit with a diagnosis that could represent a serious complication of an untreated bacterial infection (e.g. acute rheumatic fever, head and neck abscess, intracranial abscess, Lemierre syndrome, mastoiditis, meningitis, pneumonia, sepsis, etc.) will be extracted from study site EHRs and reported to the Board.

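### The safety chart review asks whether earlier antibiotics would have helped, but none of its three grades can answer yes, so probable harm shares a grade with merely possible harm

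*Protocol*

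**What the plan says.** Protocol Section 7.1 counts return visits within 30 days that carry a diagnosis of concern. Of these, "a random sample of 20% of cases will be generated for chart review". The task is described as "chart review by site physicians to determine the possibility of study interventions interfering with proper diagnosis and treatment of a patient".

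The question and the form of the answer are then fixed: "Cases will be examined to determine whether earlier antibiotics would have improved the outcomes and classified as one of the following". The first grade is UNLIKELY; the second and third are "early antibiotics MAY HAVE improved the course, UNCERTAIN if earlier antibiotics would have improved the course". No other grade is listed, and the text does not say how the second and third differ.

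Section 9.3 says that the board "is granted the power to recommend discontinuation of the study to each study IRB, if safety concerns are found".

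**The concern.** The question put to the reviewer is whether earlier treatment would have changed the outcome. A scale for that question needs a grade at each end and a place for charts that cannot be judged. This scale has an end for no but none for yes. A complication that the reviewer attributes firmly to a withheld antibiotic is recorded in the same words as one where a benefit is merely conceivable.

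The two remaining grades also overlap. Someone who thinks that antibiotics may have helped is normally also uncertain whether they would have. Two reviewers with the same opinion of the same chart could choose differently, and each would be following the form.

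What is at stake is how the safety review can be read. The board is asked to recommend whether the study should continue. A set of MAY HAVE grades made up of near-certain harms and a set made up of remote possibilities would look alike to it.

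**Working it through.** The protocol states no sample-size, power or error-rate figure on this point, so there is no figure to reproduce. The check sets the question against the permitted answers and then looks at what else reaches the board.

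**Question.** Section 7.1: "Cases will be examined to determine whether earlier antibiotics would have improved the outcomes".

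**Permitted answers.** By direction:
- Affirm that earlier antibiotics would have helped: 0 of 3.
- Lean against: 1 of 3 (UNLIKELY).
- Indeterminate: 2 of 3 (MAY HAVE, UNCERTAIN).

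**Mapping from opinion to grade.** A reviewer can hold one of four opinions:
- Thinks benefit not likely: UNLIKELY.
- Thinks benefit possible: MAY HAVE or UNCERTAIN; the form does not decide.
- Thinks benefit probable or clear: MAY HAVE, as the strongest grade available.
- Cannot judge from the chart: UNCERTAIN, by a natural reading that the form does not state.

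So the second and third opinions can fall into the same grade, and the second can fall into two. From the table of grades, the number of probable harms cannot be recovered.

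**Other information that reaches the board.**
- Sections 7 and 9.3: data on 30-day return visits with a possible serious complication go to the board. This does not depend on the grade.
- Section 7.3: adverse events are defined as the number and rate of such returns.
- Section 7.4: unanticipated events go to the ethics board and to the DSMB, which then decides on continuation.

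These routes carry events and rates. None of them records whether an individual complication was due to a missing antibiotic. A pneumonia after a respiratory infection is a listed diagnosis, but the diagnosis alone does not say that an antibiotic would have prevented it. Because such complications are listed in advance, they may also not count as unanticipated under Section 7.4. The graded review is thus the only case-level judgement of cause that the protocol describes.

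**Sampling, kept separate.** With a 20% sample, each graded chart stands for 1/0.20 = 5 returns on average. The chance that none of 5 given cases is drawn is 0.8^5 = 0.33, and for 10 cases it is 0.8^10 = 0.11. These figures would be the same with three grades or four, so they do not measure the defect in the scale.

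**The case against.** The best defence is that the review is a screen. Its stated purpose is to look for the possibility of interference, and for that purpose MAY HAVE is the positive grade and UNCERTAIN can be read as unable to judge. If withheld antibiotics caused complications, charts would move from UNLIKELY to MAY HAVE, and the board would see that shift beside the return-visit counts. This stands in part: the signal is blunted, not removed. It does not fully answer the point, because the same section poses the question as would have, and the reading that separates the two indeterminate grades appears nowhere in the text.

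A reader might infer more than the documents support:
- That clear harm cannot be reported to the board. Sections 7, 7.3 and 9.3 show that the events are reported regardless of grade.
- That the board would see the same table with or without harm. MAY HAVE counts and return rates could both rise.
- That one harm filed as MAY HAVE hides about five. The factor of five comes from the sampling fraction, and the charts not drawn still enter the counts of returns.
- That the graders know the arm and lean towards UNLIKELY. Section 7.1 says only that they are site physicians. Section 4.3 has the enrolled clinicians told their site's assignment, but nothing says that the reviewers are enrolled. The justification note in Section 5.2 and Appendix D records a decision to prescribe, so it would mostly be absent where an antibiotic was withheld. No direction of bias is shown.

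**Conclusion.** The point holds for the scale. Section 7.1 fixes a set of grades that cannot answer the section's own question: none of the three affirms benefit from earlier treatment, and two are not separated from each other. The graded review therefore cannot distinguish probable from merely possible harm.

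The size is limited. The review is one part of the safety monitoring and covers a 20% sample. The underlying events reach the board by other routes, and the primary comparison is not affected. No numerical effect on any estimate can be given.

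The conclusion assumes that the three listed grades are the whole form, which is how the sentence reads. Since the protocol itself sets the scale and does not leave it open, this is a matter of what the document states, not of detail deferred to an analysis plan. That masking of the reviewers is not stated is a secondary remark and does not carry the point.

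**What to change.** In Section 7.1, make three changes:
- Add a fourth grade, LIKELY, worded in parallel with the existing UNLIKELY grade.
- State that UNCERTAIN is reserved for charts with too little information to judge, so that MAY HAVE means a real but less than probable benefit.
- State that the number of charts in each grade is reported to the DSMB with the return-visit counts.

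The cost is one added line and one definition on the review form, and one small table in the safety report. If charts have already been graded on three levels, those marked MAY HAVE or UNCERTAIN would need a second look.

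As an optional addition, charts could be read by a physician outside the index clinic where the existing reviewers allow it. The protocol does not say how many reviewers there are, so whether this is practicable cannot be judged from the document. The change to the scale does not depend on it.
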